**Data collection:**

The data collection team will consist of a clinician to take anthropometric assessments, therapists to assess for CP severity, research assistants equipped with skills in data collection, and community mobilisers chosen from the catchment districts.

Once the caregiver-child pairs are enrolled, the research assistants will use a designed locally translated structured questionnaire to record identifying and demographic data: i) the child’s demographics, feeding difficulties, other reported health conditions and recorded anthropometry ii) the primary caregiver’s socio-demographic and economic characteristics. Severity of cerebral palsy will be assessed by trained therapists using the Gross Motor Function Classification System[^20^](#_ENREF_20). Feeding difficulties will be assessed based on parent /caregiver reports using on responses to questions on feeding extracted from an informal questionnaire previously designed by the CURIE study for clinical assessments. Parental/caregiver reports have historically been used as a measure of feeding and or oral motor status in individuals with CP.

**Randomization and blinding:**

**Randomization of participants from the CURIE (Akwenda) intervention study**: Eligible children with CP in the intervention group of the CURIE intervention study will be randomly assigned to receive PFT conditions so as to create the “both PD and PFT”, and “only PFT” conditions, as these individuals will receive PFT by default of the CURIE study. Likewise, participants in the CURIE control group will be randomly assigned to receiving, the “only PD condition”, and the “control” (neither PD nor PFT) condition.

**Randomization of participants from other organisations:** Since not all the CURIE intervention study participants may be eligible to participate (malnourished), other eligible caregivers and their children with CP sampled from elsewhere in the study site will be allocated to either the PFT or control groups of the CURIE study arms based on home village vicinity to make up the required sample for each of the four experimental conditions. Research assistants will be provided with the allocation of all participants after the baseline survey.

In order to avoid contamination, participants in the CURIE-intervention study have been allocated to clusters depending on the village where they reside. Neighboring villages were clustered together to reduce contamination between groups resulting in two geographically defined groups matched for age, sex and motor function. Given the similarity in study sites of the CURIE- study and this study, participants in our study will be allocated based on the already determined CURIE-intervention or control group village clusters as earlier described to avoid contamination. Participants in the control condition will be on waiting list to receive the PFT intervention later owing to the design of the wider CURIE study arrangement.

**Blinding:** Evaluators will be blinded on group allocations so that parent facilitators and caregivers do not report their subjective outcome measures differently. A group of independent outcome assessors (evaluators), not involved in the intervention, will administer the outcome measures after the interventions. These examiners will be blinded to group allocation to avoid reporting bias.

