**Sample size estimation:**

1. **Sample size estimation in a between subjects 2x2 factorial design (Bonnet,2016)**

**
[figure not shown]
**

In order to estimate a main effect in a between-subjects 2x2 factorial design at 95% confidence, at desired confidence interval width of 2.0, and a planning value of 8.0 for the average within group error variance, the contrast coefficients are 0.5, 0.5,-0.5 and-0.5, and the sample size required per group is approximately 31.

1. **Sample size estimation using two proportions:**

The PD program has been reported to increase weight of ≥200g in 12 days among 87% of participants in Burundi [^10^](#_ENREF_10). Based on the prevalence of malnutrition (<-2sd in any of HAZ,WAZ,BMIZ) among the CURIE CP population based cohort reported as 64% as per the 2015 assessments. Assuming the previously reported effect of the PD program, we hope to reduce malnutrition in the CP child population to about 29%, at α =0.05, and power (1-β) =0.8. After imputing these parameters into a Stata program to estimate sample size for individual randomization, of a two proportions test, the estimated total sample size is 62: Hence 31 participants per each of the four arms. Therefore for a 2x2 factorial trial, assuming a 1:1:1:1 allocation, 124 participants will be required for the study with 32 participants in each of the four conditions.

Participants in this study will include eligible caregivers of children with CP participating in the wider CURIE intervention study (Akwenda). In order to account for those that may not be malnourished from the CURIE study sample, additional caregivers of malnourished children with CP will be recruited from community-based organizations (CBOs) operating within the study setting including EKISA ministries and MUSANA community health centre. The CURIE intervention study has got two arms (PFT and Control) separated as village clusters based on geographical proximity and balanced by age, and GMFCS level. This study will utilize the available CURIE intervention clusters to avoid contamination. Details of participant recruitment from different CBOs are displayed below.

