**8.0 Study strengths and limitations**

To the best of our knowledge, this is the first experimental study to test the effect of the positive deviance strategy on the nutritional status of children and youth with CP in low-income countries (LICs). The other strength of this study is that the use of home visiting for data collection will allow for a naturalistic assessment of need and observation of the opportunities and barriers the caregiver may face with regards to feeding a child with CP. This will enable the immediate demonstration of advice ‘in situ’, and also help to build trust between the researchers and the families. However, this study had some limitations. Participant selection was primarily within the existing Akwenda/CURIE study two arm structure, and thus allocation of participants to study conditions was not completely random, which increased the potential for non-equivalent study groups and a high risk of bias. However, the difference in groups observed in some baseline factors was adjusted for during statistical analysis to determine the independent main effects of the PD and PFT interventions.

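### The protocol specifies no stratification or blocking for PD, its only randomised factor, and the planned ANOVA has no age or GMFCS term

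*Protocol*

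**What the plan says.** **How PFT is set.** PFT is not randomised here. Under Randomization and blinding, "participants in our study will be allocated based on the already determined CURIE-intervention or control group village clusters". Recruits from other organisations "will be allocated to either the PFT or control groups of the CURIE study arms based on home village vicinity". The Akwenda groups are described under Sample size estimation as "separated as village clusters based on geographical proximity and balanced by age, and GMFCS level", and under Randomization and blinding as "resulting in two geographically defined groups matched for age, sex and motor function".

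**How PD is set.** In the Akwenda intervention group, eligible children "will be randomly assigned to receive PFT conditions so as to create the “both PD and PFT”, and “only PFT” conditions". In the other group, "participants in the CURIE control group will be randomly assigned to receiving" PD alone or neither intervention. No stratification, blocking, pairing or minimisation is named for either split.

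**What is known at baseline.** The Data collection section records the child's demographics, and therapists grade motor severity with the GMFCS. On timing, "Research assistants will be provided with the allocation of all participants after the baseline survey".

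**Analysis.** Data management and analysis plans a two-way ANOVA for PD, PFT and their interaction, with pairwise or LSD comparisons, and names no covariates. Section 8.0 says that group differences seen in some baseline factors were adjusted for. Table 1 plans 31 per cell, 62 per PD level.

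**The concern.** The protocol treats age and motor function as worth balancing, but describes that balancing only for the factor that is not randomised. PD is the factor whose effect randomisation can protect, and nothing is said about balancing it.

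Age in particular is likely to matter. Participants are 2-24 years old and the primary outcome is a fixed gain in grams, which is a very different proportional gain for a toddler and for a young adult. With no age or GMFCS term in the ANOVA, that variation stays in the error term. Choosing covariates after seeing which baseline factors differ leaves the model open until the data are in. At stake are the precision of the PD estimate and how convincing it looks if the PD groups turn out visibly different.

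The randomisation method also has to be settled before allocation. A later analysis plan can add covariates but cannot change how PD was assigned.

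**Working it through.** **1. The plan's group size.** Inputs from Sample size estimation: 64% v 29%, two-sided alpha 0.05, power 0.80.

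n = [1.96·√(2·0.465·0.535) + 0.842·√(0.64·0.36 + 0.29·0.71)]² / 0.35² = 30.7, so 31 per group.

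The interval-width route gives 4·8·Σc²·(1.96/2)² with Σc² = 4·0.25 = 1, that is 30.7, again 31. The figure reproduces. The same section also mentions 32 per condition, but 4·31 = 124 matches the stated total and Table 1, so 31 is used below.

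**2. Chance imbalance under random assignment with equal groups.** The standard error of the difference in a standardised covariate is √(2/n).

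| Contrast | SE (SD units) | One covariate ≥0.25 SD | Either of two ≥0.25 SD | Either of two ≥0.5 SD |
|---|---|---|---|---|
| PD main effect, 62 v 62 | 0.180 | 16% | 30% | 1.1% |
| One PFT side, 31 v 31 | 0.254 | 32% | 54% | 9.6% |

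Across both sides and two independent covariates (four comparisons), at least one reaches 0.25 SD in 79% of trials and 0.5 SD in 18%.

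**3. In years and percentage points.** The protocol gives neither the age distribution nor the GMFCS mix. Assume ages uniform over 2-24 (SD = 22/√12 = 6.35 years) and 40% in GMFCS IV-V.

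- 62 v 62: SE of the age difference = 6.35·0.180 = 1.14 years. P(≥1.5 years) is about 19%, and P(≥15 points in severity) is about 8-10%. For either, 1 − 0.81·0.91 ≈ 26%; simulation gives 25-27%.
- 31 v 31: SE = 6.35·0.254 = 1.61 years. P(≥2 years) is about 21%, and P(≥20 points) is about 9-12%. Either in one side is about 28-31%. At least one of two sides is 1 − 0.72² to 1 − 0.69², about 48-52%; simulation gives 49-52%.

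The age thresholds are modest: 1.5 years is 1.5/6.35 = 0.24 SD and 2 years is 0.31 SD.

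**4. What restriction does.** Pairing on GMFCS band and age within each side brought both rates in step 3 to about 0%. It cut the SD of the 62 v 62 age difference from about 1.2 to about 0.4 years. Blocks of four in age-by-severity strata (also assuming half the children in the older age group) cut the chance of a severity gap of 10 points or more within a side from about 37% to 0.1%.

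**5. What model terms do.** If age and GMFCS explain a share R² of outcome variance, the standard error is multiplied by √(1 − R²). R² = 0.10 gives a 5% reduction and R² = 0.40 gives 23%. This gain comes from the covariates in the model. Once they are there, balancing adds only a few per cent of variance.

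**6. Why the two changes go together.** After close balancing, an unadjusted test has a true error rate of about 2·[1 − Φ(1.96/√(1 − R²))]: 3.9% at R² = 0.10 and 1.1% at R² = 0.40, in place of 5%.

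**The case against.** The strongest reply is that nothing here is stated wrongly. Genuine randomisation is valid without stratification, its error rate already covers chance imbalance, and section 8.0 mentions baseline adjustment. Much of this stands, and several stronger readings should be set aside.

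- **That PD is assigned without balancing.** A reader might infer this, but the protocol is silent. It gives no method, so blocks or strata are not excluded.
- **That a large imbalance is likely for the PD effect.** At 62 v 62 a difference of 0.5 SD on either of two covariates has about a 1% chance. The figure of about one half comes from taking the worst of four 31 v 31 comparisons at modest thresholds.
- **That a PD effect could not be told from an age difference.** Under random assignment the PD test is unbiased; precision and face validity are what suffer.
- **That the trial would gain much power.** Any such gain comes from adjustment under an assumed R². With the plan's own 64% v 29%, a 62 v 62 comparison already has about 98% power.
- **That section 8.0 concedes the point.** Its phrase "which increased the potential for non-equivalent study groups and a high risk of bias" concerns selection through the two-arm Akwenda structure, hence PFT, and not the randomised PD split.
- **That PFT is therefore balanced here.** The matching describes the Akwenda groups, not their malnourished subset plus new recruits.

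The timing statement also dates when research assistants receive allocations, not when they are generated. A complete baseline list at allocation is plausible but not stated.

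The reply does not dispose of the mismatch over covariates. Adjustment tied to observed differences is a weaker plan than fixed terms, and the analysis section contains neither. An analysis plan not shown may name covariates, but it cannot supply the randomisation method.

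**Conclusion.** The point holds as a worthwhile improvement; it is not an error that invalidates the trial. No restriction is specified for the one randomised factor, and the protocol's two statements on covariates do not match.

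The cost is moderate: roughly a one-in-four chance of a visible age or severity difference at 62 v 62, and about one in two somewhere at 31 v 31. Both rest on the assumed uniform ages and 40% severe GMFCS. The recoverable precision is 5-23% of the standard error if R² is 10-40%, an assumed range for a linear model such as the planned ANOVA. Nearly all of it comes from prespecified terms. Stratified blocking adds little precision, but it removes most of the visible imbalance and controls group sizes. If each side of 62 were split by coin flip, the two groups would differ by six or more in 53% of trials.

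**What to change.** 1. **Data management and analysis (main gain).** Prespecify baseline age and GMFCS band (for example I-III and IV-V) as terms in the model for the PD and PFT effects. Bring section 8.0 into line, so that adjustment no longer depends on which differences are observed.
2. **Randomization and blinding (small further gain).** State that PD is randomised within each PFT side in small blocks stratified by GMFCS band and age, from a computer-generated list produced after these two values are recorded. State that recruits from other organisations enter the same procedure. Blocks keep the cells at or close to Table 1's 31. If the whole side is listed first, randomising within consecutive pairs gives exactly 31 v 31.

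**Cost.** About one sentence in each section and a short randomisation script, with no extra participants, visits or measurements. Allocation must wait for age and GMFCS, and at this size only two or three balancing factors are practical.

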**Data management and analysis.**

Descriptive statistics will be performed by tabulation of the summary means of the individual condition levels and baseline social demographic characteristics of the children and their caregivers. Participants’ characteristics will be presented in frequency tables. A two-way analysis of variance (ANOVA) will be performed to test the independent main effects of PD and PFT, and the effect of interaction of both PD and PFT. Factor levels will be compared by a pairwise comparison of treatment means (standard error of a difference) or a fisher’s least significant difference (LSD) test. This analysis will be done in both intention to-treat and per-protocol assumptions. All analysis will be expressed in 95% two sided confidence intervals and a p-value of <0.05 will indicate statistical significance.

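### PFT follows two pre-set geographic village groups and is not randomised, so its ANOVA main effect and every cross-PFT comparison are confounded with area

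*Protocol*

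**What the plan says.** Under Randomization and blinding, the protocol describes how the parent study formed its arms: "Neighboring villages were clustered together to reduce contamination between groups resulting in two geographically defined groups". These groups are said to be matched for age, sex and motor function. Under Sample size estimation the two arms are described as "separated as village clusters based on geographical proximity and balanced by age, and GMFCS level".

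Three further statements in Randomization and blinding fix PFT status in this trial:
- CURIE families in the intervention group form the two PFT conditions "as these individuals will receive PFT by default of the CURIE study". Random assignment within each CURIE group decides only whether a family also gets PD.
- Families recruited elsewhere are "allocated to either the PFT or control groups of the CURIE study arms based on home village vicinity".
- In general, "participants in our study will be allocated based on the already determined CURIE-intervention or control group village clusters".

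The analysis in Data management and analysis is: "A two-way analysis of variance (ANOVA) will be performed to test the independent main effects of PD and PFT". It adds the interaction and pairwise comparisons of the cells, two-sided, with p<0.05 as significant. No area, village or cluster term is named.

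One of the two sample size calculations is expressly made to "estimate sample size for individual randomization". Neither uses an intracluster correlation or a design effect.

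Study design calls the trial quasi-randomised. Section 8.0 admits that "allocation of participants to study conditions was not completely random" and that the risk of bias is high. It then says that adjustment for some baseline factors served to determine the independent main effects of PD and PFT.

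**The concern.** A 2x2 factorial ANOVA treats its two factors alike. Here they are not alike. PD is assigned at random within each geographic group, at least for CURIE participants. PFT is settled by where the family lives.

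Any difference between the groups that affects growth over three months therefore enters the PFT estimate. The ANOVA judges that estimate against child-to-child variation only, so its interval is too narrow and its p-value too small. A real difference between places could be reported as a PFT effect.

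The same holds for any pairwise comparison between a PFT cell and a non-PFT cell. That includes both interventions versus neither, and PD only versus PFT only. The latter is the head-to-head that the Study Implementation plan describes when it says PD is to be evaluated against the caregiver training.

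**Working it through.** **1. The protocol's own sample size.** Inputs from Sample size estimation: 64% and 29% malnourished, two-sided alpha 0.05, power 0.80; and, for the precision method, error variance 8.0 and interval width 2.0.
- Two proportions, no continuity correction: n = [1.96·√(2·0.465·0.535) + 0.8416·√(0.64·0.36 + 0.29·0.71)]² / 0.35² = 30.7, so 31 per group and 62 in total.
- Precision: n = 4 · 8.0 · (4 · 0.5²) · (1.96/2.0)² = 30.7, so 31 per group.

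Both stated figures reproduce, on the basis of independent, individually randomised children.

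**2. Structure of the PFT contrast.** Table 1 has 31 per cell, so 62 children at each PFT level. If each level is one area, PFT and area are the same indicator variable. An area term cannot be fitted beside PFT, and an area-level analysis has 2 − 2 = 0 residual degrees of freedom. Of the six pairwise cell comparisons, only two stay within a PFT group; the other four cross it.

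**3. Type I error if each PFT level is one area.** The documents give no intracluster correlation (ρ), so a range is assumed. With total variance 1, the true variance of the PFT difference is 2ρ + 2(1−ρ)/62, while the ANOVA uses 2(1−ρ)/62. The ratio is V = 1 + 62ρ/(1−ρ), and the true type I error is 2[1 − Φ(1.96/√V)]. The effective number per PFT level is 62/(1 + 61ρ).

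| ρ (assumed) | V | Type I error | Effective n per PFT level |
|---|---|---|---|
| 0.01 | 1.63 | 12.4% | 38.5 |
| 0.02 | 2.27 | 19.3% | 27.9 |
| 0.05 | 4.26 | 34.2% | 15.3 |

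Simulating the two-way ANOVA (20,000 runs, 31 per cell, random area effect) gave 12.4%, 19.7% and 34.1% for PFT. The PD test, with PD balanced within area, stayed at 4.8% to 5.1%.

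**4. Type I error if each arm holds several separate clusters.** Assume k equal clusters per arm, m = 62/k children in each, design effect 1 + (m−1)ρ, and type I error 2[1 − Φ(1.96/√DE)].

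| k per arm (assumed) | ρ = 0.01 | ρ = 0.05 |
|---|---|---|
| 6 | DE 1.09, 6.1% | DE 1.47, 10.6% |
| 20 | DE 1.02, 5.2% | DE 1.10, 6.2% |

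**5. Interaction.** PD x PFT is the PD effect in the PFT group minus the PD effect in the other group. An area effect common to both PD levels cancels, so the inflation in step 3 does not carry over. What remains is that a true PD x PFT interaction cannot be told apart from PD working differently in the two areas.

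**6. How many families have stated PD randomisation.** The section on parent facilitator trainings gives the CURIE study 90 children, so at least 124 − 90 = 34 must come from elsewhere. If the 2015 figure of 64% still held (an assumption), about 0.64 · 90 ≈ 58 would qualify and about 124 − 58 = 66 would be new. For new recruits the protocol states placement by village but no random step for PD.

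**The case against.** The best defence is disclosure. The design is labelled quasi-randomised, Section 8.0 concedes non-equivalent groups and a high risk of bias, and geographic grouping is a deliberate guard against contamination taken over from the parent study. All of that is true. But Section 8.0 goes on to claim independent main effects after adjustment, and the analysis section keeps an ordinary p-value for PFT. The disclosure does not correct either.

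A second defence is that the groups were matched and covariates are recorded. Matching covers age, sex and motor function in the CURIE sample, and none is described for new recruits. Data collection does record socio-economic status, feeding difficulties and severity, and adjustment can reduce the part of an area difference that these explain. It would be too strong to say that adjustment can remove none of it; the sound statement is that it cannot be relied on to remove it.

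Third, a reader might infer that PFT is wholly confounded with a single area per arm, and quote only the 12% to 34% figures. The documents do not settle this. They speak of two geographically defined groups but also of village clusters in the plural, so each arm may hold several separate clusters. Inflation is then much smaller (step 4), though allocation is still not random.

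A reader might also infer that the interaction test suffers the same inflation. It does not, for the reason in step 5. Nor do the documents show which area differences exist: they report none in food access or services, tie no recruiting organisation to one area, and run both programmes over the same three months.

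**Conclusion.** The point holds, and the plan is wrong as written on it. PFT is not randomised in this trial, yet the protocol tests it as an independent, individually randomised factor. The PFT main effect and the four cross-group pairwise comparisons are confounded with area. That conclusion does not depend on any assumed correlation.

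The size of the type I error does depend on assumptions. It is about 12%, 19% and 34% at intracluster correlations of 0.01, 0.02 and 0.05 if each PFT level is one area. With 6 to 20 clusters per arm it is about 5-6% at 0.01 and 6-11% at 0.05. Neither the correlations nor the number of clusters are in the documents.

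The PD comparison is sound in this respect, provided new recruits are also randomised to PD within their group.

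**What to change.** - **Data management and analysis:** make the PD main effect, estimated within PFT group with group as a stratum, the confirmatory test.
- **Randomization and blinding:** state that new recruits, like CURIE participants, are randomly assigned to PD within their group. Without this, the confirmatory PD test has no stated random basis for a substantial part of the sample.
- **Reporting of PFT:** present the PFT main effect, the cross-group pairwise comparisons and PD x PFT as non-randomised, area-confounded estimates with confidence intervals and no efficacy claim at p<0.05. Amend the claim in Section 8.0 that adjustment yields independent main effects.
- **Standard errors:** account for village clustering, and say that this does not remove the area confounding.
- **Sample size estimation:** say that the individual-randomisation figure supports the PD comparison only.

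The changes are to wording and the analysis specification, with no change to the sample size. The cost is a weaker PFT conclusion, much of which Section 8.0 already concedes. The aims in the Introduction and the Study Implementation plan, which promise an evaluation of PFT in its own right and jointly with PD, must be reworded to match.
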